**Fig. 1 Fig1:**
[figure not shown]
Flow of participants through the RCT

All outcomes are participant-reported. Participants complete outcome assessments via electronic survey (REDCap) or paper-based (returned via mail for the minority that may request this). In addition, all participants record attendance at, and travel information about, physiotherapy consultations using a log book which is mailed back to research staff. As a reminder, research staff contact any participant who has failed to submit a survey and/or return a log book by the due date. Every effort is being made to minimize loss of data, including collection of primary outcome data over the telephone if necessary.

Immediately upon receipt of the signed consent form and completed baseline survey, a participant is randomized to either video-conferencing or face-to-face consultations with the trial physiotherapist of their choice (usually selected on the basis of geographical location). Participants are provided five physiotherapy consultations over a 12-week intervention period. Research staff book the first two consultations on behalf of the participant with the physiotherapist’s clinic at mutually agreeable times. Thereafter, the physiotherapist and participants arrange subsequent bookings together at the conclusion of each consultation.

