#### Consultations

In both trial arms, five consultations are offered with the physiotherapist over 3 months (at approximately weeks 1, 2, 4, 7, 10), each lasting 30 min except the first which is 45 min. Participants are asked to complete an electronic pre-consultation survey prior to their first physiotherapy consultation, which ascertains information about their knee symptoms, previous treatments, activity levels and personal goals. This survey is forwarded to the physiotherapist prior to the first consultation.

Table 1 provides an overview of the main components of each physiotherapy consultation. Consultations have been informed by the Behaviour Change Wheel [20] (including behaviour change techniques relevant for exercise and physical activity [21, 22], Table 2) and based on the research team’s prior research into exercise and physical activity for knee OA [11, 23–27]. In summary, physiotherapists aim to prescribe an individualised exercise program comprising 5–6 strengthening exercises to be performed at home three times/week, including two quadriceps exercises, one hip/gluteal exercise, one hamstrings/gluteal exercise, one calf exercise, and one other as appropriate. Exercises are selected from an Exercise Booklet containing 37 exercises in total (Table 3), many with a range of potential variations to make them harder or easier as required. The intensity for the strengthening exercises is aimed at 5–7 out of ten (or, “hard to very hard”) on the modified Borg Rating of Perceived Exertion (RPE) scale [28] for strength training. Review and modification of the strengthening program occurs at each consultation. Progression is guided by American College of Sports Medicine principles [29] via adjustments to repetitions, direction, and speed of movements; increasing resistance; and/or changing stance surface.

**Table 1 Tab1:** Outline of the main components of each of the five consultations with the physiotherapist

	Initial consultation (45 mins)- WEEK 1	Consultation 2 (30 mins)- WEEK 2	Consultation 3 (30 mins)- WEEK 4	Consultation 4 (30 mins)- WEEK 7	Consultation 5 (30 mins)- WEEK 10
**Assessment**	15 mins	5 mins	5 mins	5 mins	5 mins
	Introduction and setting expectations	Checking in … .	Checking in … .	Checking in … .	Checking in … .
	Review pre-consultation survey- choose questions for future reassessment.	- changes in knee pain	- changes in knee pain	- changes in knee pain	- changes in knee pain

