**5. Balance (if appropriate)**			
**Tandem stance**	Weight- bearing	B1. Maintain balance in tandem stance	**Progression:** remove hand support (if required), slowly raise arms in the air, eyes closed
**Natural stance**	Weight- bearing	B2. Maintain balance whilst tapping opposite foot forwards & backwards	
**Single leg stance**	Weight- bearing	B3. Maintain balance in single leg stance	**Progression:** Increase hold time up, slowly raise arms up and down, eyes closed

Physiotherapists also work with the patient to devise an individualised physical activity plan, with the aim of increasing physical activity to, or maintaining it at, recommended levels [30]. Participants use a wearable activity tracker to assist this and the physiotherapist and participant devise individualised step goals that are reviewed and modified (if required) at each consultation. Participants are encouraged to use the “Knee Plan and Log Book” for recording both their strengthening exercise program and physical activity plan after each consultation, and monitoring progress for discussion with the physiotherapist at the next consultation. Education about OA and its management occurs at all sessions, including discussion about the role of exercise and physical activity, including barriers to adherence and strategies for overcoming obstacles. Table 1 outlines the different education topics at each consultation.

Participants are encouraged and advised how to independently progress their exercise program and their physical activity plan between consultations, and beyond, once the physiotherapist consultations have ceased. Participants are encouraged to continue with their strengthening exercises and physical activity plan after the physiotherapist consultations have finished, up until the final outcome measurements are collected at 9 months. Participant use of monitoring and tracking tools (“Knee Plan and Log Book”; wearable activity tracker) is encouraged during the consultations, and beyond, to facilitate ongoing adherence to strengthening exercise and physical activity.

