#### Co-interventions

Participants self-report any co-intervention use (medications for knee pain and any other treatments for knee OA) at baseline, 3, 6 and 9-months as part of the custom-developed survey collecting health service usage data (see below).

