#### Adverse events

Participants who experience any adverse outcomes are instructed to discuss these with their physiotherapist, who institutes appropriate advice and/or changes to the strengthening exercise program and/or physical activity plan. Any risks to participants are likely to be minor and transient. In this trial, adverse events are defined as any problem experienced in the study knee or elsewhere in the body deemed by the participant to be a result of the exercises, physical activity plans and/or advice given by the physiotherapist AND at least one of i) that caused increased pain and/or interfered with function for 2 days or more, and/or ii) resulted in the participant seeking treatment from a health professional. Adverse events are ascertained by survey questions to participants at 3 and 9 months. The number and type of events are reported.

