#### Cost-effectiveness outcomes

##### Health service usage

Participants retrospectively recall their health service usage for their knee pain and/or as a result of trial participation over 3-month intervals. Participants complete a custom survey to indicate the frequency of visits to health care providers for their knee pain, use of prescription and over the counter medication, injections, hospitalisation and investigative procedures at baseline, 3, 6 and 9 months.

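### After month 3, adverse events are asked about only once, at month 9, although the same participants already complete a 6-month survey with 3-month recall

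*Protocol article*

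**What the plan says.** The Adverse events section fixes the source and the times: "Adverse events are ascertained by survey questions to participants at 3 and 9 months". An event is a problem that the participant attributes to the exercises, activity plan or advice and that meets at least one of two criteria. One is a problem "that caused increased pain and/or interfered with function for 2 days or more"; the other is seeking treatment from a health professional. The promised output is descriptive: "The number and type of events are reported".

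The Consultations section places the five consultations at about weeks 1, 2, 4, 7 and 10. Table 1 has the physiotherapist ask about adverse events at consultations 2 to 5. The text after Table 3 encourages participants to continue strengthening and physical activity "up until the final outcome measurements are collected at 9 months".

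A further survey goes to the same participants. Co-interventions are collected "at baseline, 3, 6 and 9-months as part of the custom-developed survey collecting health service usage data". The Health service usage section gives that survey's look-back: "Participants retrospectively recall their health service usage for their knee pain and/or as a result of trial participation over 3-month intervals".

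**The concern.** From about week 10 to month 9 participants exercise and progress their programme without a scheduled consultation. The month-9 survey is the only named source of adverse events for months 3 to 9, so a problem in month 4 must be remembered and attributed to the programme about five months later. A flare lasting two days qualifies, and a short, self-limiting episode of that kind is easily lost to recall.

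The 6-month survey does not fill the gap. Its listed content is visits, medication, injections, hospitalisation and investigations. It may show events that led to care, but it is not named as an adverse-event source and does not cover problems that meet only the two-day criterion.

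At stake is the completeness of the number and type of events reported for months 3 to 9. The Background in the Abstract gives the lack of robust evidence on safety as part of the case for the trial, so an undercount that is cheap to avoid is worth avoiding.

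**Working it through.** **Schedules side by side**

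| Period | Adverse-event survey | Service-use survey | Scheduled consultations |
|---|---|---|---|
| Months 0–3 | month 3 | month 3 | to about week 10 |
| Months 3–6 | none | month 6, 3-month recall | none |
| Months 6–9 | month 9 | month 9, 3-month recall | none |

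The gap between adverse-event surveys after month 3 is 9 − 3 = 6 months. With a month-6 question it falls to 3 months. The plan gives no figure for adverse-event capture, so there is none to reproduce.

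**Illustrative size**

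Assumed inputs, not in the documents:
- forgetting at a constant rate L of 0.02, 0.10 or 0.20 per month;
- events spread evenly over months 3 to 9;
- 6-month survey completion p of 0.50, 0.85 or 1. The 0.85 borrows the 15% loss to follow-up in Sample size calculations.

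The figures apply to participants who complete the 9-month survey.

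The share of events still recalled over a span of T months is A(T) = (1 − exp(−LT)) / (LT).

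| L | A(6) | A(3) |
|---|---|---|
| 0.02 | (1 − e^−0.12)/0.12 = 0.942 | (1 − e^−0.06)/0.06 = 0.971 |
| 0.10 | (1 − e^−0.6)/0.6 = 0.752 | (1 − e^−0.3)/0.3 = 0.864 |
| 0.20 | (1 − e^−1.2)/1.2 = 0.582 | (1 − e^−0.6)/0.6 = 0.752 |

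The current plan captures A(6). Suppose a month-6 question is added, and the month-9 question reaches back to the last completed adverse-event survey. Then capture = p·A(3) + (1 − p)·A(6), which is never below A(6). The share of those captured events that the current plan misses is 1 − A(6)/capture.

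| p | Capture at L = 0.02, 0.10, 0.20 | Share missed by current plan |
|---|---|---|
| 0.50 | 0.956, 0.808, 0.667 | 1.5%, 6.9%, 12.7% |
| 0.85 | 0.966, 0.847, 0.727 | 2.5%, 11.2%, 19.8% |
| 1 | 0.971, 0.864, 0.752 | 2.9%, 13.0%, 22.6% |

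At p = 0.85 the gain is 2.4, 9.5 or 14.4 events per 100 true events.

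**Why the look-back must be conditional**

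If the month-9 question covered only the last three months for everyone, months 3 to 6 would be lost for anyone who missed the 6-month survey. Capture would be A(3)(1 + p)/2. Since A(6) = A(3)(1 + e^−3L)/2, that beats the current plan only if p exceeds e^−3L, that is 94%, 74% or 55%.

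**Participants too late to benefit**

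The Timelines section gives recruitment from November 2019 to August 2021; even accrual is assumed. Participants past month 6 on the publication date of 7 August 2020 were randomised by 7 February 2020.
- Earliest start and end (1 November 2019 to 1 August 2021): 98/639 = 15.3% of 394, about 60.
- Latest start and end (30 November 2019 to 31 August 2021): 69/640 = 10.8% of 394, about 42.

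**The case against.** The strongest case against is that this is a choice and not an error. Pain, function, quality of life, self-efficacy and adherence are also followed up at 3 and 9 months, and the 6-month contact is described only for service use and co-interventions. The safety question concerns video consultations, which end at about week 10. The period in which the arms differ has its own month-3 survey and the physiotherapists' checks at consultations 2 to 5. The more consequential later events should leave a trace in the 6-month service-use data. The article expects risks to be minor and transient. The six-month look-back is inferred, because the question wording is not printed and Table 4 is not shown. The percentages depend almost wholly on an assumed forgetting rate, and the model ignores over-reporting and misdating. Changing the survey mid-trial would leave two ascertainment schemes in one count and need an ethics amendment.

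Much of this stands. There is no contradiction in the text, the percentages are illustrative, and with no event rate given they cannot be turned into a number of missed events. The contrast during the consultation period is not in question. But the objection disputes no fact about the schedule. The consultation checks stop before month 3, and service-use items cannot show an event that met only the two-day criterion. Pain and function are scored over the past week, so a six-month gap between surveys does not lengthen their recall as it does for adverse events. An amendment to add a few questions is routine.

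**Conclusion.** The point holds, as a modest improvement to consider. Adverse events in months 3 to 9 depend on one survey at month 9, while a 6-month contact with shorter recall goes unused for them. Under the assumptions above, the current plan would miss between 1.5% (2% monthly forgetting, 50% completing the 6-month survey) and 22.6% (20% monthly forgetting, full completion) of the events that the changed plan would capture. The lower end is trivial and the upper end is an upper bound.

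The model leaves out one further gain: participants who answer at month 6 but are lost by month 9 would contribute months 3 to 6.

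The effect is incomplete descriptive counts of mostly minor events in both arms. No between-arm bias is shown. The co-primary outcomes, the sample size and the months 0 to 3 safety contrast are unaffected. The conclusion rests on the inferred six-month look-back.

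**What to change.** 1. Add the existing adverse-event questions to the 6-month survey.
2. Word the month-9 question to cover the period since the participant's last completed adverse-event survey, which is month 3 if the 6-month survey was missed.
3. Count an event reported at both times once.

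The existing reminder, under which "research staff contact any participant who has failed to submit a survey", would apply to the 6-month survey. The telephone back-up in Procedures overview is named only for primary outcome data, so it should not be relied on here.

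The cost is a few items in a survey already sent, a check for duplicate reports, conditional wording at month 9 and a routine ethics amendment. The downsides are a slightly longer survey and a mixed schedule: if the change had been made at publication, about 42 to 60 of 394 participants would already have been past month 6. Randomisation is 1:1 and stratified by physiotherapist, so the mix should be similar in both arms. The report should say when the question was added.

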#### Cost-effectiveness outcomes

##### Health service usage

Participants retrospectively recall their health service usage for their knee pain and/or as a result of trial participation over 3-month intervals. Participants complete a custom survey to indicate the frequency of visits to health care providers for their knee pain, use of prescription and over the counter medication, injections, hospitalisation and investigative procedures at baseline, 3, 6 and 9 months.

##### Participant time

Participants record their total time spent per consultation (including travelling to/from, waiting and consultation time) in an Appointment Log Book. Mean time for consultations is reported.

##### Physiotherapist time

Physiotherapists record their total time spent per consultation (excluding note-taking and appointment scheduling). Mean time for consultations is reported.

##### Participant travel

Distance travelled to attend consultations, along with mode of transport (including vehicle descriptions and need for another person to accompany (if applicable)), is recorded by participants in an Appointment Log Book. Mean distance travelled, mode of transport and need for another person is reported.

##### Descriptive measures

A range of participant self-reported descriptive measures are recorded at baseline including recruitment source; data collection mode; height; body mass; body mass index; age; gender; duration of symptoms; geographical residential location; education level; current employment status; problems (pain, aching, discomfort or stiffness) in other joints; comorbidities (via the Self-Administered Comorbidity Questionnaire [45]); expectation of treatment outcome (rated on a 5-point ordinal scale with anchors of “no effect at all” to “complete recovery”); confidence using technology in day to day life; frequency of use of a range of technologies; beliefs about different models of physiotherapy care delivery and previous experience with different models of physiotherapy care delivery.

### Sample size calculations

Sample size is based on detecting non-inferiority of video consultations relative to face-to-face at 3 months after randomisation. For change in NRS pain, a non-inferiority margin (NIM) of 0.95 units was chosen as this is less than the lowest of the range (1.0–2.0 units) [46, 47] reported as the minimum clinically important difference (MCID) by people with chronic pain, and less than the MCID of 1.75 units (extrapolated from a 100 mm visual analogue scale (VAS)) [48] for OA by clinician consensus. For change in WOMAC subscales, a NIM of 8 mm on VAS versions of WOMAC (score 0–100) is used in drug non-inferiority RCTs [49], as it is less than the MCIDs of 9.1–9.3 mm [50, 51]. We are using the Likert version of WOMAC (scored 0–68) for function, thus our NIM for change in function is 5.44 units (extrapolated from 8 mm). Assuming standard deviations (SD) of changes from baseline of 2.8 and 15 units for pain and function respectively and correlations of 0.3 between baseline and follow-up [11, 26], 15% loss to follow-up, 90% power, and a one-sided 2.5% significance level, we need 197 people/arm for change in pain and 172/arm for change in function, a total of 394 people.

### Statistical analysis plan

The a priori statistical analysis plan is described below. Any future amendments to this statistical plan will be documented, dated and explained in an electronic log kept by the research team, which will be made available upon request. A biostatistician will perform data analyses.

Consistent with OARSI guidelines [52], non-inferiority will be assessed using the per-protocol dataset (including only those randomized participants who attended ≥3 consultations). Between-group differences in mean change in pain and function (baseline minus follow-up) will be compared using linear regression modelling adjusted for baseline and the stratifying variable of physiotherapist. If a physiotherapist treats participants at two locations, two separate terms for that physiotherapist, corresponding to each location, will be included. Non-inferiority will be demonstrated if the lower bound of the two-sided 95% CI for between-group difference (video-conferencing minus face-to-face) is above − 0.95 for change in pain and/or − 5.44 for change in function, at 3 months. 95% CIs correspond to testing the null hypothesis of non-inferiority at a one-sided significance level of 2.5%. Due to difficulties with their interpretation, *p*-values associated with non-inferiority hypotheses are not commonly reported and will not be reported here [53]. Multiple imputation will be used to impute missing data, and an intention-to-treat analysis (including all participants in their randomised groups) will be conducted to help assess robustness of conclusions (sensitivity analysis). Given that participants with knee OA seek physiotherapy care for different reasons, we will interpret and report findings transparently and separately for each co-primary outcome. For example, if we demonstrate non-inferiority of video consultations with respect to function but not pain, we will conclude that video consultations are non-inferior to face-to-face care for improving function but are inferior for pain relief in people with knee OA. Patients seeking care, and physiotherapists delivering care, will then be fully informed about benefits, and limitations, of video consultations compared to face-to-face care with respect to the different co-primary outcomes. If non-inferiority of a co-primary outcome is demonstrated, superiority of the outcome will then be assessed using the intention-to-treat dataset and declared if the lower bound of the two-sided 95% CI for between-group difference exceeds zero.

Secondary outcomes will be assessed using data from all participants (i.e. the intention-to-treat sample) and confidence intervals will be interpreted using the superiority framework since we have not pre-defined any NIMs for these outcomes. Linear regression models will be fit to compare continuous outcomes; proportional odds models to compare improvement based on global change; and Poisson or negative binomial regression models to compare count outcomes as appropriate. Assumptions will be assessed using standard diagnostic plots and methods. Since these are all secondary analyses, *p*-values for these assessments will not be adjusted for multiple comparisons [54, 55]. In addition, the outcomes of participant time, physiotherapist time and travel time will be compared between treatment groups using the superiority framework, similarly to other secondary outcomes.

Irrespective of the outcomes of the non-inferiority analysis, we will conduct exploratory analyses to evaluate moderation of the effect of video-conferencing versus face-to-face consultations on primary outcomes by pre-specified potential moderators, i) experience with online video platforms; ii) geographical residence; iii) beliefs about physiotherapy care delivery; and iv) confidence using technology. This will be assessed by including appropriate interaction terms between the moderators and the intervention term, where the superiority framework will be applied for interpreting results. The a priori hypotheses to be tested are:
i.Participants who are less frequent users of video platforms will have less improvement in primary outcomes with video consultations (relative to face-to-face), compared to participants who are more frequent users.ii.Participants who don’t live in major city areas will report greater ease of access, and reduced participant-level time and financial costs (secondary outcomes) with video consultations (relative to face-to-face), compared to participants who live in major cities.iii.Participants who believe that video consultations are less effective for managing musculoskeletal problems will report less improvement in primary outcomes with video consultations (relative to face-to-face), compared to those who believe video consultations are more effective.iv.Participants who are less confident with using technology will report less improvement in primary outcomes with video consultations (relative to face-to-face), compared to participants who are more confident.

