Knee OA is mostly managed in primary care settings, with physiotherapists frequently involved in provision of care. Physiotherapy is traditionally provided during face-to-face consultations in the clinic. However, for many people, access to physiotherapy is hampered by geographical isolation and/or limited physiotherapy services. This is particularly a problem in regional and remote areas where services are often limited or non-existent. Face-to-face consultations also pose an infection risk for both the physiotherapist and the patient. This has been highlighted by the COVID-19 pandemic where many physiotherapy practices across the globe have restricted or ceased face-to-face consultations and instead shifted towards telehealth, in order to safeguard the health of both patients and staff.

We conducted the first RCT evaluating efficacy of video consultations with a physiotherapist for exercise management of knee OA [11]. We recruited 148 older people around Australia and compared video consultations (delivered by 8 different physiotherapists) combined with a self-directed online pain coping skills program, versus online education. Findings showed that the intervention significantly improved knee pain and physical function by clinically meaningful amounts at 3 months, and that benefits were sustained at 9 months. Furthermore, nested qualitative research showed that video consultations were acceptable to both patients and physiotherapists [12]. Patient convenience, flexibility, empowerment to self-manage and positive therapeutic relationships were emphasised by both patients and physiotherapists. Patients were very satisfied with the care they received and believed it was effective for them personally. These findings reflect survey data in people with knee OA [13] and in patients attending hospital-based physiotherapy screening clinics [14], as well as RCT findings in patients following joint replacement [15]. Collectively, research indicates most patients are willing to engage in video consultations for chronic musculoskeletal conditions. However, there is no research comparing the effectiveness of video-conferencing with physiotherapists to face-to-face consultations for people with knee OA.

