#### Mode of physiotherapy delivery

Face-to-face consultations – participants allocated to this group attend all of their consultations with the physiotherapist in the physiotherapist’s clinical practice rooms. Participants travel to and from the clinic at their own expense. Physiotherapists use their usual clinical methods for teaching the strengthening exercise program (ie demonstration, watching and correcting participant technique). Consultations are audio-recorded using digital audio recorders and uploaded by the physiotherapist to a secure password-protected cloud-based system.

Video consultations - participants allocated to this group attend all of their consultations using the video-conferencing facility of Zoom (Zoom Video Communications, Inc., USA), a commercial cloud-based system accessible from any internet-connected computer, laptop or mobile device. Physiotherapists consult from their clinic using a lap-top or desk-top computer, whilst participants are based at their home (or elsewhere if preferred). Instructions for accessing and downloading Zoom are provided to participants and participants are encouraged to independently set themselves up in readiness for their first consultation. Physiotherapists are given access to a bespoke website containing a video library of all exercises contained within the “Exercise Booklet” so that they can provide real-time demonstration of exercises to participants during video-conferencing, using the share-screen feature of Zoom. Participants do not have access to the online video library outside of the consultations. Video-conferencing consultations are video-recorded via Zoom and files are stored on a secure password-protected cloud-based system.

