#### Attendance at consultations

Attendance at each consultation is recorded by physiotherapists in treatment notes, and by participants in an “Appointment Log Book”. The number of consultations attended, number of consultations cancelled/rescheduled, and number of consultations that were a “failed to attend” are reported throughout the 3-month intervention period.

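### The per-protocol set that decides non-inferiority requires three consultations attended but not that they were in the allocated mode, so any switching between modes would dilute the comparison unseen

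*Protocol article*

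**What the plan says.** All references are to the protocol article.

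- **Arms (Mode of physiotherapy delivery).** Face-to-face: "participants allocated to this group attend all of their consultations with the physiotherapist in the physiotherapist’s clinical practice rooms". Video: "participants allocated to this group attend all of their consultations using the video-conferencing facility of Zoom". Content, number of visits and physiotherapists are common to both arms, so mode is the only randomised contrast.
- **Dose (Consultations).** In both arms, "five consultations are offered with the physiotherapist over 3 months".
- **Deciding set (Statistical analysis plan).** Non-inferiority is judged on the "per-protocol dataset (including only those randomized participants who attended ≥3 consultations". Attendance is the only criterion named. The section presents itself as the a priori plan, so the definition is fixed here and not deferred.
- **Robustness check (same section).** "an intention-to-treat analysis (including all participants in their randomised groups) will be conducted to help assess robustness of conclusions (sensitivity analysis".
- **What is recorded (Attendance at consultations).** "The number of consultations attended, number of consultations cancelled/rescheduled, and number of consultations that were a “failed to attend” are reported". Neither this list nor the items under Treatment fidelity include the mode of each consultation.
- **Setting (Background).** Because of the pandemic, "many physiotherapy practices across the globe have restricted or ceased face-to-face consultations and instead shifted towards telehealth". Under Timelines, recruitment began in November 2019 and was expected to finish in August 2021.

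**The concern.** A per-protocol set in a non-inferiority trial is meant to remove deviations that make the arms look alike. Here the deviation that does so most directly is receiving the other arm's mode of delivery, and the rule does not test for it. A face-to-face participant whose five visits all took place by Zoom would breach the arm's own definition and still count as per-protocol face-to-face.

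The intention-to-treat analysis does not help, because it also keeps that participant in the face-to-face arm. Agreement between the two analyses would then say nothing about switching.

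The article's own facts make switching feasible. Every participant must have an internet-connected device and is mailed Zoom instructions. Every physiotherapist is trained in video delivery and treats both arms. Participants must also be willing to travel to the clinic, so a move from video to clinic is possible too. At stake is a claim of non-inferiority when video is in truth worse by the margin or more.

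**Working it through.** **Inputs (Sample size calculations).** Margins 0.95 (pain) and 5.44 (function); SD of change 2.8 and 15; baseline to follow-up correlation 0.3; 15% loss; 90% power; one-sided 2.5%.

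**Step 1: reproduce the stated sample size.** n per arm = 2(1.960 + 1.282)² × SD²(1 − 0.3²) / margin².

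- Pain: SD = 2.8 × √0.91 = 2.671, so n = 167; 167/0.85 gives 197.
- Function: SD = 15 × √0.91 = 14.309, so n = 146; 146/0.85 gives 172.

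Both match the article.

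**Step 2: standard error.** With 167 analysed per arm, SE = SD × √(2/167), which is 0.292 for pain and 1.566 for function.

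**Step 3: dilution.** Let video be truly worse by exactly the margin M. Suppose a share c of the analysed face-to-face arm gets the full video effect. The expected difference shrinks from −M to −M(1 − c). Non-inferiority is declared when the lower 95% limit exceeds −M, so

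P(false non-inferiority) = Φ(c × M / SE − 1.96).

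Example, pain at c = 20%: 0.20 × 0.95 / 0.292 = 0.65, and Φ(0.65 − 1.96) = 9.5%.

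| c (assumed) | Expected pain difference | Error, pain | Error, function |
|---|---|---|---|
| 0% | −0.95 | 2.5% | 2.5% |
| 5% | −0.902 | 3.6% | 3.7% |
| 10% | −0.855 | 5.1% | 5.3% |
| 20% | −0.76 | 9.5% | 10.3% |
| 30% | −0.665 | 16.2% | 17.9% |

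A simulation of 20,000 trials per scenario for pain, with 167 per arm, gave 5.1%, 9.2% and 15.7% at 10%, 20% and 30%.

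**Step 4: what could be masked.** A true pain deficit of 0.95/(1 − c) would be expected to appear as exactly 0.95. At c = 20% that is 1.19, above 1.0, the lower end of the range of minimum important differences that the article cites.

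**Step 5: partial and reverse switching.** If a switched participant gets only a fraction f of the other mode's effect, c is replaced by c × f. Twenty per cent switched with half the effect therefore gives the 10% row. Switching from video to clinic adds its own share to c in the same way.

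**Step 6: cost of excluding switchers.** If a share c of the face-to-face arm is removed, SE = 2.671 × √(1/167 + 1/[167(1 − c)]). Power for pain at a true difference of zero falls from 90.1% to 88.6% (c = 10%), 86.5% (20%) and 83.9% (30%).

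**The case against.** **The wording may already imply allocated mode.** Each arm is defined by its mode and no route for switching is described, so the three consultations could be read as those of the participant's own arm. That reading is possible. But the rule does not state it, and an analyst applying it literally would keep switchers. A reader should equally not infer that the plan deliberately counts visits in the other mode; it is silent.

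**No switching is documented.** The remarks on the pandemic concern practices worldwide, and the only effect on this trial that the article mentions is on recruitment rates. Visits could have been paused or cancelled instead, and anyone left with fewer than three is already excluded. This stands. A reader might infer that the 2.5% error rate is not kept, and the document does not support that as a flat statement. It follows only if participants switch and video is truly worse.

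**The figures combine unfavourable assumptions.** They put the truth at the margin, assume the switch rate, and give switchers the full video effect. With visits at about weeks 1, 2, 4, 7 and 10, a mid-course switch moves only some of them. Excluding low attenders also raises the SE above 0.292, which lowers the inflation. All of this stands, and the table is best read as a set of upper scenarios.

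**Excluding by mode has its own bias.** In a pandemic scenario the exclusions fall mainly on the face-to-face arm in particular months, while concurrent video participants stay. That disturbs the balance over time given by permuted blocks within physiotherapist. This also stands, and it is why the attendance-only set should still be reported.

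**An attendance rule suits a pragmatic trial, and an article may leave deviations to a fuller document.** This carries less weight, because the section fixes the set by a stated rule and calls itself the a priori plan.

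**Conclusion.** The point holds as a conditional one. The set that decides non-inferiority does not require receipt of the randomised mode, and the stated sensitivity analysis shares the gap. If the modes differ and some participants switch in either direction, both estimates move towards zero.

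The size is unknown, because the article gives no switch rate. With video truly worse by the pain margin and full replacement of the effect, the one-sided error would be about 5%, 9.5% and 16% at 10%, 20% and 30% switched; function is similar. With no switching it stays at 2.5%, and with no true difference there is nothing to dilute. The article supports neither a claim that switching took place in this trial nor a claim that the error rate is already lost. It does support a correction before unblinding, since the gap concerns the only factor that was randomised.

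**What to change.** Before unblinding, and through the dated amendment log that the Statistical analysis plan section already provides for:

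1. Define the per-protocol set as participants who attended at least three consultations in their allocated mode. With five visits offered, three is already a majority, so no further rule about the predominant mode is needed.
2. Take mode from sources already collected: the consultation notes, the audio or Zoom recordings, and the travel entries in the Appointment Log Book.
3. Report the attendance-only set alongside, and report the number switched by arm and calendar period.
4. Adjust for calendar period, or examine it, in the mode-restricted analysis.

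The cost is a one-line change of definition, one derived mode variable per consultation, a slightly smaller set (power as in the last step of the working), and some post-randomisation selection, mainly in one arm. Some dilution remains, since a participant with two of five visits in the other mode still qualifies. If nobody switched, the two sets coincide and nothing is lost.
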